**Key SBCC Messages:**
Eat at least five different food groups every day (grains, white roots and tubers and plantains; pulses (beans, peas and lentils); nuts and seeds; dairy products (milk, yogurt, cheese); meat, poultry and fish; eggs; dark green leafy vegetables; vitamin A-rich and other fruits and vegetables) during pregnancy and the lactation period.Use 250 g (two cups) of Super Cereal every day during pregnancy and the first 6 months of lactation and avoid sharing with family members.Initiate breastmilk to newborn within 1 h of birth, continue exclusive breastfeeding until 6 months of age and introduce nutritionally adequate and safe complementary (semi-solid and solid) foods at 6 months together with continued breastfeeding up to 2 years of age or beyond.Give your child a variety of food groups every day (grains, roots and tubers; legumes and nuts; dairy products (milk, yogurt, cheese); meat, fish, poultry, liver/organ meats; eggs; Vitamin A-rich and other fruits and vegetables) during 6–24 months of age. Do this a minimum of two times for breastfed infants aged 6–8 months, three times for breastfed children aged 9–23 months and four times for non-breastfed children aged 6–23 months.Give one sachet of LNS to your child every day from 6–24 months and avoid sharing with other children.Wash your hands with soap before preparing food, before eating, before feeding a child, after handling feces/diapers or using the latrine and keep the cooking utensils clean to prevent frequent illnesses.

### 1.3. Primary Outcome

The impact of nutritional supplementation during the ‘1000 days’ on the reduction in the prevalence of stunting (LAZ < −2 SD) among children under two years of age in the intervention areas compared to control areas.

### 1.4. Secondary Outcomes

Impact on low birth weight (birth weight < 2500 g) by improving maternal nutrition.Impact on reduction in the prevalence of wasting (WLZ < −2 SD) and underweight (WAZ < −2 SD) in children under two years of age.Improvement in IYCF practices.Improvement in minimum acceptable diet and minimum dietary diversity among PLW.Improvements in care-givers’ knowledge, attitudes and practices related to infant and young child feeding.Improvement in mean hemoglobin concentrations in children and PLW.Improvement in maternal BMI z-scores.Formulation and adoption of local recipes for complementary feeding of children aged 6–23 months using locally available nutritious foods.

## 2. Experimental Design

### 2.1. Study Design

A quasi-experimental pre-post study design with a control group will be used to evaluate the study outcomes. We propose to compare the intervention and control group between the pre- and post-intervention assessments to isolate the effect of the intervention by difference-in-differences estimates. Repeated cross-sectional baseline and endline surveys will be conducted in both the intervention and control districts. The intervention districts in province Badakhshan will be subjected to a robust implementation and close monitoring of the SNF provision, together with SBCC activities delivered through health facility staff, CHWs and mother care groups, while the control districts in province Takhar will receive the routine standard of care available in the area.

Before launching the intervention, formative research will be conducted on the acceptability and appropriate use of nutritional supplements and to help inform the SBCC strategies related to supplements, maternal diet during pregnancy and lactation and IYCF practices. A literature review will be conducted to adapt the relevant themes and existing national guidelines on maternal, infant and young child nutrition (MIYCN) to the local context of Afghanistan. Qualitative methods will be used for formative research including focus group discussions (FGDs) and key informant interviews (KIIs) with target population and relevant stakeholders and direct observations (DOs) for most common household foods recipes for the PLW and children aged 6–23 months.

Program monitoring, evaluation and learning will be conducted to examine the processes including the quality of implementation, the acceptability of the program components, the identification of potential barriers and to learn how to enhance the program’s effectiveness through ongoing operational improvements. This will be conducted by the AKU and study partners on a monthly basis to assess the distribution of supplements, the number of mother groups formed, the key SBCC messages delivered, food demonstrations, the development of local recipes, the monthly mother group meetings, the CHW meetings held on various SBCC activities and the identification of model families (Figure 1).

### 2.2. Study Area

Afghanistan has an estimated population of 32.9 million, consisting of 34 provinces and 398 districts in 2019. About 71% of the population lives in rural settings [37]. Badakhshan province is located in the farthest north-eastern part of the country bordered with Tajikistan, Pakistan and China. This study will be conducted in two districts in Badakhshan (Shuhada and Shari Buzurg), while the control will be in the two districts Rustaq and Worsaj in Takhar province. Takhar province is selected as the control location for the study because these two districts are almost similar in terms of accessibility, socio-economic conditions, food consumption practices, geography and ethnicity. On the other hand, Badakhshan is selected as an intervention area because the selected districts are under the coverage of implementing partners AKHS and AKF and an additional layer of close monitoring by the AKU, the WFP and the MoPH will also be possible. The Badakhshan province is selected for this study because the maternal child health characteristics are poor, but the province is generally less affected by the political instability affecting the rest of the country.

## 3. Procedures

### 3.1. Development of Data Collection Instruments

In collaboration with study partners and local staff, the Aga Khan University will develop topic guides on nutritional intake for mothers during pregnancy and lactation, IYCF practices and the acceptability of and perceptions toward the Super Cereal and LNS-MQ among all participants. We will explore the contextual elements such as interaction with the health care system, livelihoods and other aspects of local culture. We will develop semi-structured, KII [38] and FGD [39] guides with major questions, sub questions and probes in English and will translate into local language, e.g., Dari. To ensure the accuracy of translation, these guides will also be back translated from Dari to English by core study team members [40]. A direct observation guide will also be developed to observe local household food recipes for PLW and children 6–23 months of age by the field researchers [38].

The baseline/endline household survey questionnaire will be developed and used to collect data on household size, socio-demographic characteristics, hand washing, maternal and child anthropometric measurements, maternal and child hemoglobin measurements, the minimum dietary diversity for pregnant and lactating women, antenatal and postnatal care, IYCF practices, maternal knowledge about IYCF, child immunization, morbidity and care seeking, exposure to other interventions and the household food insecurity access scale.

### 3.2. Hiring and Training of Research Staff

We will hire and train a local team of four field researchers (two male and two female), fluent in English and in the local language, i.e., Dari for formative research. The minimum qualification for field research will be 14th grade education with 2–3 years of experience in qualitative research. The training will include principles of qualitative research, in-depth interviewing techniques and FGD and DO techniques. The team will be trained in five days. After training, the field researchers will have three days of practice in the field to test the interview guides for understanding with participants of similar socioeconomic characteristics who will not participate in real data collection. The interview guides will be adjusted if needed after field testing. During field practice, each field researcher will conduct two KIIs, two FGDs and two DOs. The data from the KIIs and the FGDs will be digitally recorded. The recorded data will be transcribed verbatim in the local language and then will be translated verbatim into English. During the practice, field researchers will also transcribe and translate verbatim [38,41] (from the local language into English) the content of the KII and the FGD and write their DO reports in English.

A total of eight data collection teams will be hired locally from Badakhshan and Takhar for the baseline and endline survey. The minimum qualification for data collectors and team leaders will be 12th and 14th grade education, respectively. Each team will consist of two female data collectors and one male team leader. The household survey teams will receive five days of hands-on training on study objectives, informed consent, methods, data collection tools, anthropometric measurements and spot hemoglobin testing. All the questionnaires will be pre-tested in the field and changes will be incorporated accordingly before the actual data collection. The questionnaires will be developed in English and will be translated into Dari (the local language) and then back translated into English by an independent person to compare the translated document with the original for accuracy and quality. A one-day field test will be carried out before initiating field work. As part of the training, all field staff will be trained on anthropometric measurements with additional days for team measurers to continue to refine their skills. The training will include both in class explanations and exercises with field practice. A study manual will be provided to each team leader, which will include instructions, methodology and sampling strategy.

### 3.3. Sample Size and Sampling for Formative Research

To define the sample size, the concept of data saturation will be used. Data saturation is defined as the point where the data being collected do not provide new insights into the research questions [38,41,42]. The number of participants required to reach data saturation varies depending on the objectives of the study and the complexity of the topics being explored. However, we are planning to conduct four FGDs with pregnant and four with lactating women. We will also conduct two FGDs with mothers-in-law and two with the fathers of children under 24 months of age. Eight KIIs will be conducted with CHWs, four with health care providers, four with focal persons of study partners and four with community leaders. A total of fourteen DOs will be held in households for observation of the most common recipes for PLW and children 6–24 months of age. Data will be collected in the catchment areas of seven intervention group health facilities. A purposive sampling method will be used to select the participants and will ensure representation of the different health facilities and participants.

### 3.4. Sample Size for Programme Evaluation Surveys

A total of 2912 children <2 years with their mothers (1456 per group per survey) were estimated to provide reasonable precision (80% power, 95% confidence interval, design effect of 1.5 and response rate of 95%) for baseline and endline surveys based on a 13% reduction in the prevalence of stunting in children under two years old in the intervention areas, as compared in the control areas at endline.

To calculate the sample sizes for anemia (1125 mothers and 810 children per group per survey) with 80% power, a 95% confidence interval, a design effect of 1.5 and a response rate of 95% were estimated to detect a relative 20 and 13% decline in the prevalence of anemia among mothers and in children at endline, respectively.

All pregnant and lactating mothers with children under two years of age will be eligible for baseline and endline surveys. Eligible participants will be identified through two levels.

At health facilities, a list of pregnant women who accessed ANC services and breastfeeding mothers who accessed PNC and childcare services will be prepared.At the community level, a list of PLW and children will be prepared through CHWs. These will include those PLW and children who were not captured at the health facility level.

The baseline and endline surveys will follow a two-stage cluster sampling design. In the first stage, 30 clusters will be randomly selected from each intervention and control area (60 total) using probability proportional to the population size (PPS) sampling design. The data collection teams will prepare a list of all the PLW with children under two years old in each selected cluster and required households from each cluster will be randomly selected for the survey. There will be no replacement in case of refusal. The same sampling design will be used at endline.

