### 1.1. Description of Stunting Prevention Programme

As part of the Country Strategic Plan, the World Food Program (WFP) planned to implement a stunting prevention program in collaboration with the Ministry of Public Health (MoPH) through its Public Nutrition Department, Afghanistan in two selected districts of Badakhshan with stunting rates (HAZ < −2SD) of >45% [34]. These two districts were considered based on high stunting prevalence, access to beneficiary communities, the existence of implementing partners providing complementary health/nutrition and security access to implementation sites. The program will emphasize an appropriate nutrition support in the ‘1000 days’ window of opportunity with special focus on proven effective nutrition interventions such as appropriate breast feeding, complementary feeding, micronutrient supplementation, malnutrition treatment and prevention and hand washing. This will, therefore, take the form of an integrated approach ensuring the targeted beneficiaries are supported to access nutrition assistance as well as other complimentary interventions provided in-kind by study partners and will be promoted through SBCC. The program will target pregnant and lactating women (PLW) and children aged 6–23 months, but will also engage fathers, grandfathers, grandmothers and community players that influence maternal, infant and young child nutrition (MIYCN).

The program will include monthly distributions of SNF for PLW and children aged 6–23 months and counselling for their mothers and caretakers on the appropriate use of SNF. All the trainings and SBCC messages will be developed based on formative research on the knowledge, attitudes, practices and barriers to optimal IYCF practices. During the project implementation, emphasis will be placed on the adoption of the locally formulated complementary foods as well as the application of knowledge and practices promoted through the SBCC activities as part of the exit strategy and ensuring a long-lasting impact of the project.

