## 4. Results

The primary study finding will be the impact of intervention on the prevalence of stunting among children under two years old in the intervention group compared to the control group. Secondary findings will be the prevalence of low birth weight in newborns and the prevalence of wasting, underweight, anemia and IYCF practices among children under two years of age. Furthermore, we will also report the minimum dietary diversity, anemia and nutritional status among PLW. We will aim to compare the results of the intervention and the control group between the pre- and post-intervention assessments to isolate the effect of the intervention by difference-in-differences estimates.

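### Section 3.4 sizes the surveys for a two-group endline comparison, but the effect is to be estimated by difference-in-differences, so the stated 80% power is not that of the named analysis

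*Protocol article*

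**What the plan says.** Section 3.4 gives the size as "A total of 2912 children <2 years with their mothers (1456 per group per survey"), with "80% power, 95% confidence interval, design effect of 1.5 and response rate of 95"%. The effect, put at 13%, is a "reduction in the prevalence of stunting in children under two years old in the intervention areas, as compared in the control areas at endline". Section 3.4 does not give the reference prevalence of stunting, and it does not say whether the 13% is relative or absolute. The only prevalence elsewhere is in section 1.1, which refers to "two selected districts of Badakhshan with stunting rates (HAZ < −2SD) of >45" per cent. That is a lower bound for the intervention districts only.

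Section 2.1 names the effect estimate. The plan is to "compare the intervention and control group between the pre- and post-intervention assessments to isolate the effect of the intervention by difference-in-differences estimates". Section 4 repeats that the aim is to "isolate the effect of the intervention by difference-in-differences estimates", and the Abstract says the same. The Abstract and section 2.1 describe the surveys as repeated cross-sections in both the intervention and the control districts. Section 3.4 adds that endline uses the same sampling design (30 clusters per area, drawn with probability proportional to size). It does not say whether the same clusters are revisited.

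Section 3.4 also sizes anaemia at 1125 mothers and 810 children per group per survey, for relative declines of 20% and 13% at endline, with the same power, confidence, design effect and response rate.

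**The concern.** An endline comparison has sampling error from two samples. A DiD from repeated cross-sections has it from four, because the baseline difference is estimated too and is subtracted. With equal sizes and similar prevalences, the variance roughly doubles. The sample-size paragraph allows for clustering and non-response, but not for the baseline surveys.

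The districts are not randomised and lie in different provinces, so DiD is the design's protection against baseline differences and cannot lightly be dropped. If the 80% belongs to another contrast, readers will credit the primary analysis with more power than it has. A true reduction of the planned size could then be missed far more often than one time in five.

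**Working it through.** **Inputs from section 3.4:** 1456 per group per survey; 80% power; 95% confidence, taken as two-sided 5%; design effect 1.5; response 95%; 13% reduction.

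**Assumptions (not in the document):** the 13% is relative; the reference prevalence is 50%; the four samples are independent. The second and third are varied below.

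**1. Reproducing 1456 as a two-group endline comparison, 50% v 43.5%**

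- Unpooled: n = (1.96 + 0.8416)² × (0.5×0.5 + 0.435×0.565) / 0.065² = 921. Then 921 × 1.5 / 0.95 ≈ 1454.
- Pooled variance: n = 924. Then 924 × 1.5 = 1386, and 1386 / 0.95 ≈ 1459. If non-response is added as × 1.05 instead, 1455.3 rounds up to 1456.
- A relative 13% from 45% would need about 1764 (pooled), and from 48% about 1575.
- An absolute 13 points would need only about 340 to 365, so it does not explain 1456.

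**2. The same numbers under DiD**

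Effective size per cell = 1456 × 0.95 / 1.5 = 922.

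- Endline difference: SE = √[(0.25 + 0.2458)/922] = 2.32 points. Power = Φ(6.5/2.32 − 1.96) ≈ 80%.
- DiD, with three cells at 50% and one at 43.5%: SE = √[(3×0.25 + 0.2458)/922] = 3.29 points. Power = Φ(6.5/3.29 − 1.96) = 50.7%.
- Solving for 80% DiD power gives a reduction of about 9.2 points, or 18.4% relative.
- For 80% DiD power at 13% relative, the size would be about 2914 to 2922 per group per survey, about twice the plan.

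**3. Dependence on the 50%**

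For any two-group size set at 80% power, doubling the variance gives Φ(2.80/√2 − 1.96) ≈ 51%. The drop therefore does not hinge on 50%. If n is instead held at 1456, with independent samples:

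| Reference prevalence | DiD power, 13% relative |
|---|---|
| 45% | 43% |
| 50% | 51% |
| 55% | 59% |
| 60% | 67% |

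**4. Dependence on independence**

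If the same clusters are revisited, part of the cluster variance cancels. With a design effect of 1.5, that share is about 0.5/1.5 = 1/3. At 50% prevalence, multiply the DiD variance by (1 − r/3), where r is the correlation of cluster effects between surveys. Power is 54% at r = 0.25, 58% at 0.5, 63% at 0.75 and about 68% at r = 1.

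**5. Anaemia**

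No anaemia prevalence is given. Two-group calculations return about 1125 mothers at roughly 34% and about 810 children at roughly 65%. Those values are back-solved. At them, DiD power is about 50% in mothers and 51 to 52% in children, if these too were two-group calculations.

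**The case against.** **The 50% is inferred.** With one free input, a match to 1456 proves little. A DiD calculation for a 13% relative reduction from about 67% also returns 1456, so the size could in principle already be for DiD. This stands as a caution about the exact figure. It is the less likely reading, because section 3.4 places the comparison at endline and nothing in the document suggests 67%. A reader might also say that 1456 is reproduced exactly. It is, but only if non-response is added as × 1.05. The other routes give 1454 or 1459, so close agreement is all that can be claimed.

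**Revisited clusters would help.** This also stands, since the document leaves the point open. At 50% prevalence it lifts power to about 68% at most. At 60% prevalence with perfect correlation the shortfall would close: SE = √[(3×0.24 + 0.2495)/922 × 2/3] = 2.65 points, and power = Φ(7.8/2.65 − 1.96) ≈ 84%. But that needs perfect correlation and a prevalence at which the endline sizing would not give 1456.

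**Other text fits the sizing.** The primary outcome in section 1.3 compares intervention with control areas without naming DiD, and section 3.7 does not mention DiD. Both are true. Neither names another effect estimate, and the Abstract and sections 2.1 and 4 name only DiD.

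**An unseen analysis plan may recover precision by adjustment.** It may, but nothing in the article claims this. The point here is a stated power that does not belong to the stated estimate, not missing detail.

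**Anaemia is weaker ground.** Section 3.4 speaks of a decline at endline without naming the control group, so even the contrast that was sized is unclear. The anaemia figures are conditional on that reading.

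**Conclusion.** The mismatch is in the text. Section 3.4 sizes an endline comparison, and the Abstract and sections 2.1 and 4 estimate a DiD with about twice the variance. The 80% is therefore not the power of the named analysis.

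If the 13% is relative and the reference prevalence is 50%, DiD power is about 51% with independent samples and up to about 68% with perfectly correlated revisited clusters. The detectable DiD effect with independent samples is about 9.2 points, not 6.5.

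A reader might infer that the study's true power is 51%. The document does not support so firm a statement: it gives neither the reference prevalence nor the handling of clusters, and with 1456 and independent samples the figure runs from 43% at 45% prevalence to 67% at 60%. A reader might also infer that a null result will be taken as proof that the programme fails, but nothing in the article says how a null would be read.

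**What to change.** Keep the enrolment. In section 3.4:

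- State the reference stunting prevalence actually used, and that the 13% is relative. The sponsor should supply the prevalence; the 50% inferred here should not be printed as the sponsor's assumption unless it was.
- State whether the endline clusters are redrawn or revisited and, if revisited, the correlation assumed.
- Replace the 80% claim with the DiD power for the 13% reduction, or with the effect that DiD can detect with 80% power, on those inputs. If the reference is 50% and the samples are independent, that is about 51% power for 13% relative, or 80% power for about 18% relative.
- Restate the anaemia sizes in the same way, with their reference prevalences and the contrast intended.

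The cost is protocol wording. The downside is that the stated power, or the detectable effect, becomes less favourable.

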### 1.2. Intervention Package and Delivery Mechanism

The interventions will focus on the provision of SNF to eligible beneficiaries and SBCC messaging delivered through existing health systems, mobile health teams and CHWs at community levels. All children aged between 6–23 months will receive locally produced lipid-based nutrient supplement–medium quantity (LNS-MQ) and PLW will receive Super Cereal during the study.

*Super Cereal—Wheat Soya Blend with Sugar:* Super Cereal is prepared from heat-treated wheat and whole soya beans, sugar, vitamins and minerals by the WFP. This product is pre-packed and available in 1.5 kg packets. The WFP food safety and quality control unit is responsible for the quality assurance of the product during the program period. A monthly ration of 7.5 kg of Super Cereal (250 g per day) will be provided to pregnant women during pregnancy and to lactating mothers for the first 6 months [35].

*Lipid-based Nutrient Supplement–Medium Quantity (LNS-MQ):* LNS-MQ or Wawa Mum is made with heat-treated oil seeds, pulses, cereals, milk powder, sugar, vegetable oils, vitamins and minerals. Wawa Mum is manufactured from ingredients that are fresh, of good quality and free of foreign materials, infestations and substances hazardous to health. It does not contain any ingredients of animal origin, except dairy products. A daily sachet of 50 g of Wawa Mum will provide 255 Kcal. A monthly ration of 30 sachets will be provided to children during 6–23 months of age. The WFP food safety and quality control unit is responsible for the quality assurance of the product during the program period [36].

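### Section 3.4 admits only children whose mother is pregnant or lactating, so some under-twos fall outside the primary-outcome sample and endline eligibility partly depends on a behaviour the programme promotes

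*Protocol article*

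**What the plan says.** Three statements in section 3.4 set who can be surveyed.

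- Eligibility: "All pregnant and lactating mothers with children under two years of age will be eligible for baseline and endline surveys".
- Second-stage frame: "The data collection teams will prepare a list of all the PLW with children under two years old in each selected cluster". PLW stands for pregnant and lactating women.
- Facility list: besides pregnant women seen at antenatal care, it covers "breastfeeding mothers who accessed PNC and childcare services".

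The section adds that the endline survey uses the same sampling design.

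The target population is wider. The primary outcome (1.3) is stunting "among children under two years of age in the intervention areas compared to control areas", with no condition on breastfeeding. The supplement rule in 1.2 begins "All children aged between 6–23 months will receive locally produced" and does not depend on breastfeeding either. The key messages include a feeding frequency of "four times for non-breastfed children aged 6–23 months", so weaned children are a recognised part of the target group. The same messages promote complementary foods from 6 months "together with continued breastfeeding up to 2 years of age or beyond".

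**The concern.** Two problems follow from the wording.

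**Coverage.** Children whose mother is neither pregnant nor breastfeeding any child, and children with no mother in the household, receive the supplement and belong to the outcome population, but no listing rule admits them.

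**Selection after treatment.** The surveys are repeated cross-sections, so eligibility is set afresh at endline, after at least 12 months of counselling in the intervention districts. If that counselling prolongs breastfeeding, more children enter the endline frame in that arm only. Difference-in-differences removes selection that is stable over time. It does not remove selection that the intervention itself shifts.

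At stake are the stunting estimate and the breastfeeding part of the IYCF secondary outcome. The second is affected more directly, because current breastfeeding is one of the ways into the sample.

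**Working it through.** **1. Scale of the planned effect.** Section 3.4 gives 1456 per group per survey for a 13% reduction, with 80% power, a 95% confidence level, design effect 1.5 and response rate 95%. The prevalence is not stated. Assuming 50% falling by a relative 13% to 43.5%, the two-proportion formula (pooled variance under the null, two-sided 5%) gives 924. Then 924 × 1.5 × 1.05 = 1455.3, rounded up to 1456 (dividing by 0.95 instead gives 1459). The implied effect is 50 − 43.5 = 6.5 points. This is an inference, used below only for scale.

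**2. Who is outside the frame.**

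| Child under two | In the outcome population (1.3) | Can be sampled (3.4) |
|---|---|---|
| Breastfed by the mother | yes | yes |
| Weaned, mother pregnant | yes | yes |
| Weaned, mother breastfeeding a younger child | yes | yes |
| Weaned, mother neither pregnant nor breastfeeding | yes | no |
| No mother in the household | yes | no |

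**3. Possible share outside the frame (all inputs assumed).** Take ages uniform over 0–23 months, weaning only at 12–23 months with share w, and k the share of weaned children who stay in because the mother is pregnant or breastfeeding a younger child. Then x = 0.5 × w × (1 − k).

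- w = 10%, k = 30%: 0.5 × 0.10 × 0.70 = 3.5%.
- w = 40%, k = 20%: 0.5 × 0.40 × 0.80 = 16%.

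A larger k lowers these figures. Children without a mother in the household would add to them.

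**4. Shift in difference-in-differences with no true effect.** Let x be the share outside the frame at baseline, d the share of all under-twos that the programme moves into the frame, and D the stunting prevalence of excluded children minus that of included children. In-frame prevalence in the intervention area then changes by D × d / (1 − x + d), while the control area does not change.

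| x | d | D (points) | Shift (points) |
|---|---|---|---|
| 5% | 5% | +5 | 5 × 0.05/1.00 = +0.25 |
| 10% | 5% | +10 | 10 × 0.05/0.95 = +0.53 |
| 10% | 5% | −10 | −0.53 |
| 30% | 10% | +15 | 15 × 0.10/0.80 = +1.9 |
| 30% | 10% | −10 | −1.25 |

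The sign follows D. The 30% rows exceed the 16% of step 3 and mark an extreme.

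**5. The part due to age.** Assume stunting of 35% at 0–11 months and 65% at 12–23 months, equal in weaned and breastfed children within each band, and k = 30%.

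- w = 30%: (0.175 + 0.395 × 0.65)/0.895 = 48.24%.
- w = 20%: (0.175 + 0.430 × 0.65)/0.930 = 48.87%.

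The spurious change is +0.63 points. With w falling from 40% to 25% it is 47.56% to 48.56%, or +1.0 point. Standardising to the uniform age distribution gives 0.5 × 35% + 0.5 × 65% = 50% in every case, so here age adjustment removes the whole shift. Only a difference between weaned and breastfed children of the same age would survive adjustment.

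**6. Continued breastfeeding at 12–23 months.** The measured proportion is (1 − w)/[(1 − w) + k × w]. For a true rise from 70% to 80%:

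| k (assumed) | Measured before | Measured after | Measured change |
|---|---|---|---|
| 20% | 0.70/0.76 = 92.1% | 0.80/0.84 = 95.2% | 3.1 points |
| 30% | 0.70/0.79 = 88.6% | 0.80/0.86 = 93.0% | 4.4 points |
| 50% | 0.70/0.85 = 82.4% | 0.80/0.90 = 88.9% | 6.5 points |

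The level is too high and the change smaller than the true 10 points in each row.

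**The case against.** **PLW may be shorthand.** Section 3.4 sizes the survey in children under two with their mothers, and its community list covers PLW and children. Section 1.2 limits Super Cereal for lactating mothers to the first 6 months, so the article does not use lactating in one fixed sense. Section 3.2 mentions a study manual containing the sampling strategy, which is not shown. A broad reading, any mother in the 1000-day window, is therefore possible. But the article never defines the term that way, "breastfeeding mothers who accessed PNC and childcare services" points to current breastfeeding, and the community list only identifies eligible participants. If the broad meaning is intended, the sentence still needs correcting, because listing teams would act on it.

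**The bias may be small.** With 50% prevalence assumed, the standard error of the difference-in-differences is √(4 × 0.25 × 1.5/1456) = 3.2 points, so a shift of 0.6 to 1.0 point is about 0.2 to 0.3 standard errors. This stands. An adjustment for age may also be specified in an analysis plan that is not shown.

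**Stronger readings that the documents do not support.**

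- A reader might infer that all weaned children drop out. Those whose mother is pregnant or breastfeeding a younger child stay in.
- A reader might infer that the bias works against the programme and equals 10–15% of the planned effect (0.63/6.5 and 1.0/6.5). That holds only in the age-mix illustration, which age adjustment removes. If excluded children are less stunted than included ones, the sign reverses.
- A reader might infer that continued breastfeeding is close to 100% by construction. Step 6 gives 82% to 95%. Section 1.4 names IYCF practices in general, not this indicator.
- A reader might infer that nothing can be repaired once baseline is done. The age-mix part can be adjusted for, and the frame can still be widened at endline.

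**Conclusion.** The mismatch is real on the text: the frame in 3.4 is narrower than the population in 1.3 and 1.2, and endline eligibility partly depends on breastfeeding, which the programme promotes in one arm only. Using the same rule in both areas and both rounds does not cure this.

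For stunting, the conclusion is that the estimate could be biased. The documents give no weaning, repeat-pregnancy or age-specific stunting rates, so size and direction are unknown. The assumed scenarios stay below 2 points in either direction, against an inferred planned effect of 6.5 points, and a shift caused purely by age mix could be adjusted away. A within-age difference between weaned and breastfed children could not, because the excluded children are never measured.

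For breastfeeding indicators within the IYCF outcome, inflation of the level follows from the frame whenever some weaned children are excluded. The amount, such as 70% to 80% measured as about 89% to 93%, rests on the assumed k of 30%.

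**What to change.** **Before baseline listing.** In 3.4, define the second-stage frame as all children aged 0–23 months living in the selected cluster, each with the mother or primary caregiver, whatever the mother's pregnancy or lactation status. Align the eligibility sentence and the facility and community lists with it, and use the same wording at both rounds. Record current breastfeeding as a variable. Report PLW outcomes in the pregnant and lactating subset.

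**If baseline has already used the PLW frame.** List all under-twos at endline and flag those outside the PLW frame. Keep the like-for-like comparison, with age adjustment, and report the all-children estimate as a sensitivity analysis. Because those children were not measured at baseline, that estimate has no matching baseline. Some selection within age will remain and should be stated as a limitation.

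**Cost.** A wording change in 3.4 and in the listing form, with sample size and field procedure unchanged. Slightly fewer of the 1456 sampled mothers will be pregnant or lactating, against 1125 needed for maternal anaemia. At the 16% upper figure of step 3, 1456 × 0.84 = 1223 remain. The target would be missed only if more than 1 − 1125/1456 = 22.7% were neither pregnant nor lactating.
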